### Study setting

To evaluate this health care project, three participating statutory health care insurance companies (IKK Südwest, Techniker Krankenkasse, Knappschaft) work together to offer PIKKO to their insured cancer patients in the Saarland, which is the second smallest state in Germany (997,000 inhabitants). About 80 physicians (clinicians and practitioners, various specializations) in about 25 cities (different population sizes) agreed to recruit participants. The intervention is performed by specially trained PN who are located in clinical or outpatient settings.

### Eligibility criteria

#### Inclusion criteria

Patients eligible for PIKKO must comply with all of the following:
age ≥ 18 years and ≤ 90 years,diagnosis of any cancer disease (ICD-10-diagnosis group C00-C97 or D45-D48 (initial diagnosis, relapse or transition to palliative care)),current treatment by doctors from the Saarland,insured with one of the three statutory health insurance companies participating in this study.

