**Methods:**

The study population includes all cancer types, both new and existing diseases. PIKKO (with patient navigator, oncological knowledge database, specialized oncological counseling) is evaluated within a controlled, non-randomized, comparative, multicenter, longitudinal design. In addition to patient surveys, data from statutory health insurances and utilization data from the web database are collected, and interviews with patient navigators and doctors are carried out. Patients are assigned to a control (usual care) or an intervention group (u. c. + PIKKO). Primary outcome is the health related quality of life (SF-12) six months after baseline. Secondary outcomes are self-efficacy (GSE), psychological distress such as depression (PHQ-9) or anxiety (GAD-7), health literacy (HLS-EU-Q47) and patient satisfaction in health care (Qualiskope-A). Furthermore, the time course of direct costs of medical care (e.g. work disability days) and usage data of the intervention modules are analyzed. Among other statistical procedures, we use t-tests, univariate tests and growth curve models.

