### Sample size calculation

The three participating health insurance companies have a potential of 325,000 insured persons in the Saarland and their averaged prevalence of cancer (ICD-10-diagnosis groups C00-C97 or D45-D48) is 6.532%. Thus, the study population included (rounded up) 22,000 patients.

The financing of the PIKKO supply concept was calculated for a maximum of 1.800 patients per group, 3.600 patients in total. That means that 1.800 participants of the intervention group can benefit from the PN and the other intervention modules.

To evaluate the PIKKO intervention only 676 participants (338 per group) of the patient questionnaires are required to the statistical analyses. This number of cases was calculated with the program GPower version 3.1.7 [41]. The calculation is based on an expected effect of d = 0.25 for a two-sided t-test with same sized comparative groups, a level of significance of α = 0.05 and a power of 1-β = 0.9. The t-test refers to the primary outcome. We assumed that 338 patients would drop out and added this amount to the total number of included patients. As a consequence, the recruiting aim was *N* = 1014 = 676 + 338 patients (per group 507 = 338 reaching the end point + 169 dropout). The expected dropout rate was 33.3% regarding the baseline (338 of 1014) or respectively 50% regarding the patients reached the endpoint (338 of 676).

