### Statistical methods

Characteristics of control and intervention groups (e.g. age, sex, education, family situation, partner situation) will be analyzed with descriptive statistics. Since no randomization is made for ethical and research practical reasons, univariate tests are used to determine which of the above mentioned characteristics differ between the two groups. Ideally there are no significant differences between the two groups. In the case of significant differences we will compute propensity scores using the corresponding pre-treatment variables. Then, we will apply in the subsequent analyses propensity scores as stabilized regression weights to reduce bias caused by different group characteristics.

The main hypothesis of an intervention effect on psychological and physical health, self-efficacy, health care costs etc. will be proofed by the comparison of averages of intervention and control group (resp. t-tests). To estimate the corresponding regression adjusted group means we will use growth curve models. Furthermore, we will conduct subgroup analyses to identify conditional treatment effects.

For dropout analysis we will conduct a logistic regression with dropout as criterion and group assignment and baseline variables as predictors applying the regression weight mentioned above. For the time-to-event analysis we will conduct a Cox regression.

The level of significance will be α = 0.05. To validate our analyses, we will conduct the analyses with imputed missing data and without imputation.

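### The adjustment rule does not ensure that disease phase enters the comparison of two consecutively recruited cohorts, although cancer status and treatment are collected at T0

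*Protocol article*

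**What the plan says.** **Who can enter.** Inclusion criteria in the protocol article asks for a cancer diagnosis in ICD-10 groups C00-C97 or D45-D48 and adds in brackets "initial diagnosis, relapse or transition to palliative care". No interval between event and enrolment is given. The Methods part of the abstract says "The study population includes all cancer types, both new and existing diseases". The paragraph closing Exclusion criteria says that a mix of severities and disease stages is intended.

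**How groups are formed.** Under Trial design, the recruitment date alone decides the group: controls come first, intervention patients afterwards. Trial status gives 23 November 2017 to 31 October 2018 for controls and from then to 31 March 2020 for the intervention group. A further insurer joined in summer 2019.

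**How differences are handled.** Statistical methods compares group characteristics ("e.g. age, sex, education, family situation, partner situation") with univariate tests. Where differences are significant, propensity scores are computed from the corresponding variables and used as stabilized weights. Table 1 lists cancer status and treatment at T0 in both groups.

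**Planning figure.** Sample size calculation states that the insurers "have a potential of 325,000 insured persons in the Saarland", that "their averaged prevalence of cancer (ICD-10-diagnosis groups C00-C97 or D45-D48) is 6.532" per cent, and "Thus, the study population included (rounded up) 22,000 patients".

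**The concern.** In a design without randomization and with consecutive recruitment, the phase of disease at entry is an obvious clinical confounder of six-month mental quality of life. A patient just diagnosed, one in relapse, one moving to palliative care and one in stable treatment can be expected to follow different courses without any intervention. If the phase mix differs between the periods, part of that natural course appears as a PIKKO effect, or hides one.

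The eligibility wording allows a wide mix and sets no window that would hold it constant over time. The protection therefore has to come from the analysis. There the adjustment depends on a significance test, and the named examples contain no disease variable. A confounder can be missed in two ways: it is never among the tested characteristics, or it is tested, falls short of significance and is left out.

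A secondary question is whether the three events restrict eligibility or only illustrate it. The answer determines what the 22,000 represents and how the second control group is drawn. That group is defined by meeting the inclusion criteria and is taken from insurer data, and the insurer measures in Table 2 include diagnoses but no relapse or palliative transition.

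**Working it through.** **1. The planning figure.** Inputs from Sample size calculation: 325,000 insured persons and a prevalence of 6.532%.

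- 325,000 × 0.06532 = 21,229.
- 22,000 / 21,229 = 1.036. The stated figure is 3.6% higher, consistent with the disclosed rounding up to the next thousand.
- The product uses ICD group only. Age 18 to 90, the requirement "current treatment by doctors from the Saarland" and the exclusion criteria are not applied. It is therefore an upper bound on the eligible population of these three insurers, whether or not the three events restrict entry.

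**2. Does this reach the sample size?** Inputs: d = 0.25, two-sided α = 0.05, power 0.90, equal groups.

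- The exact t-test calculation gives 337.2, hence 338 per group and 676 in total.
- 676 / (1 − 1/3) = 1,014, or 507 per group.
- All stated figures reproduce, and none uses the 22,000.

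**3. The eligibility statements side by side.** Relapse and palliative transition are themselves existing disease, so the bracket and the abstract can both be true. A patient in stable treatment some years after diagnosis is covered by the abstract and by the prevalence count, but is in doubt under the bracket. This is an ambiguity, not a contradiction.

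**4. What the significance rule lets through.** Suppose phase is tested as a yes/no characteristic with 507 patients per group at T0. The smallest difference in proportions that reaches two-sided 5% significance is about 1.96 × √(2p(1 − p)/507), where p is the assumed share of patients in that phase.

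- p = 0.5: 1.96 × √(0.5/507) = 1.96 × 0.0314 = 0.062, or 6.2 percentage points.
- p = 0.2: 1.96 × √(0.32/507) = 1.96 × 0.0251 = 0.049, or 4.9 percentage points.

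Smaller differences stay out of the propensity score. If phase is not tested at all, the rule sets no limit.

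**5. Translation to the outcome.** For one yes/no phase variable, the crude bias in SD units is the difference in proportions times the difference in six-month mental score between phases. The documents give neither factor. Purely as an illustration, with an assumed score difference of 0.3 to 0.5 SD, a 6.2-point imbalance gives 0.062 × 0.3 = 0.019 to 0.062 × 0.5 = 0.031 SD. That is 7% to 12% of d = 0.25, before any reduction by the planned adjustment. The conclusion does not rest on these values.

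**The case against.** **The case for the plan.** The list of characteristics is introduced as examples, so disease variables are not excluded, and a condensed article may leave the full list to the analysis plan. SF-12 is measured at T0, and growth curve models with regression-adjusted means are planned, which should absorb part of any baseline difference. The same criterion applies to both cohorts, mixed stages are intended, and the article discloses the lack of randomization. Most of this stands. It does not remove the point, because the article does fix the selection rule: variables enter when they differ significantly. That rule is a weak safeguard for any confounder, however long the list. Adjustment for the baseline score also does not fully remove a difference in subsequent course.

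**Stronger readings that the documents do not support.**

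- A reader might infer that the eligibility statements contradict each other. They can be reconciled, as shown in the working.
- A reader might infer that the control year used up the standing pool of existing patients, leaving relatively more new events for the intervention period. The recruiting aim of 507 is 507 / 21,229 = 2.4% of the prevalent patients, which is far from depletion. If the three events do restrict entry, there is no standing pool. The additional insurer also brought in patients whom the control year had not drawn on.
- A reader might infer that recruitment would need 42% to 85% of eligible patients per year. That takes the financed maximum of 1,800 as numerator and an assumed 10% to 20% annual event share. With the recruiting aim and the same assumption, it is 507 / 4,246 = 12% to 507 / 2,123 = 24%. Recruitment has closed in any case.
- A reader might put the bias at 12% to 40% of the planned effect. That requires a 10 to 20 point phase difference and a 0.3 to 0.5 SD score gap, neither of which is documented, and ignores the planned weighting.

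**Conclusion.** The point holds as a weakness of the adjustment rule. Disease phase can differ between the two cohorts because calendar date determines the group and entry spans several phases without a window. Consecutive recruitment is the main source of this risk, and the eligibility wording adds to it. The direction is unknown. As written, the rule guarantees neither that phase is examined nor that it is kept when examined: imbalances of up to about 5 to 6 percentage points would pass as non-significant at the planned baseline size, for assumed phase shares of 20% to 50%. The effect on the primary result cannot be quantified from the documents.

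The unclear bracket and the unfiltered 22,000 are matters of clarification. They leave sample size and power untouched.

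**What to change.** **Main change, in Statistical methods.** Always include disease phase, or cancer status and treatment as recorded at T0, in the propensity score or the adjusted primary comparison, irrespective of the univariate tests. Add time since diagnosis where it was recorded; Table 1 does not show whether it was. Add a sensitivity analysis of the primary outcome by disease phase, including patients with one of the three named events as far as T0 data identify them.

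**Minor clarifications.**

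- State whether the three events restricted eligibility in practice, and within what interval if one was used.
- Apply the same definition to the second control group, or say that insurer data cannot reproduce it and what this means for the check on selection bias.
- Label the 22,000 as prevalent insured patients (21,229 before rounding), an upper bound on the eligible population of the three insurers.

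**Cost.** A few more model terms, possibly slightly more variable weights, and some wording. The T0 cancer data are already collected. New enrolment fields or a new time window are not useful, because recruitment ended on 31 March 2020.

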#### Exclusion criteria

Patients are not eligible in case of one of the following:
statutory guardianship,insufficient knowledge of the German language,very strong visual and hearing impairment,dementia or other mental limitations.

Overall, we intend to obtain a heterogeneous sample with various types of cancer, degrees of severity, stages of disease and co-morbidities in order to reflect the reality of everyday care routine including its various aspects as well as possible.

### Recruitment

To recruit physicians to participate in PIKKO, the consortium leader (IKK Südwest) organized internal (invitations to the IKK Südwest) and participated in external (health-related congresses and similar) information events. They are addressed to all physicians of different specialization that are involved in care of cancer patients: oncologists, gynecologists, urologists, general practitioners, internists, and other. The participating hospitals, clinics, and medical practice must sign a study contract to participate in the supply concept PIKKO and to recruit patients. The enrollment is conducted by physicians or trained medical staff e.g. a nurse.

For the recruitment of PN, mailings were made to all participating hospitals, clinics and practices. Up to ten persons can be trained with a two weeks course by the German Cancer Society. Target group are people who already work in the field of cancer-related health care such as oncological nurses, social workers or other non-medical staff of an oncological outpatient clinic or oncological department of a hospital.

The patients are recruited in various ways. Firstly, they can be addressed directly while attending a medical consultation (outpatient or inpatient) as long as they show the inclusion criteria. The enrollment is carried out directly. Secondly, a landing page at the internet serves as a contact point to patients who hear about PIKKO via mass media such as newspaper articles and radio program or on various events about cancer [27]. The potential participant is using a contact form and receives a phone call by his/her health insurance company. Eligibility criteria are checked and a local enrollment is arranged. Thirdly, health insurance companies can recommend their members to attend the study. The enrollment is carried out by post. And fourthly patients can actively ask their physician, statutory health insurance, the German Cancer Society, the Cancer Society of the Saarland or the evaluator. In this case the potential participant will be led to a local enrollment person.

### Intervention

PIKKO is an additional supportive care intervention with focus on communication and information. It does not replace the usual cancer treatment. Rather, it complements the usual treatment path by integrating four new modules into care.

The central module is a PN. Within PIKKO this PN is called (in German) “Onkolotse”. This is a specially trained person with medical background but not a doctor. They attend a two week training course performed by the German Cancer Society, which was exclusively composed for PIKKO. Contents are oncological medical background incl. complementary and alternative medicine, communication, psychological oncology, nutrition and cancer, physical activity and cancer, management of side effects of cancer treatment, palliative medicine, social law, use of the oncological knowledge database, self-management and privacy. The acquired skills, the own experiences, talents and empathy qualify the PN to advise and to accompany participating patients along the complex way through their cancer treatment, especially across sectoral borders of the German healthcare system. The PN also activate the patient access to the oncological knowledge database called “my pikko” (in German “Mein PIKKO”), the second module of the intervention.

“Mein PIKKO” [27] is a web based database that provides evidence-based information across all cancer entities. The provided information is easy to understand and has been specially processed for layperson. Suitability for layperson was tested by repeated usability tests and the database was adjusted if required. On the one hand this database consists of general evidence-based information about cancer such as genesis, prevention, diagnostic, treatment incl. naturopathic ways, side effects, nutrition, physical activity, psychological support or palliative care. On the other hand there is information on socio-political aspects such as health insurance, nursing care insurance, pension insurance, accident insurance, unemployment insurance, rehabilitation or state regulations. The database is provided, hosted and consistently updated (every six month) by the German Cancer Society and includes only evidence based information and other trusted material. Other features are the search for useful addresses, prepared questions for a consultation with a physician and a dictionary. Each patient (or relatives as support) has 24/7 access to the database for quality-assured information. We expect that patient education is increasing, and therefore information gaps between physician and patient will be reduced and finally shared decision-making will be improved.

The third module of the intervention is an offer for all participating patients of a specialized oncological counseling provided by the Cancer Society of the Saarland in order to identify the psychosocial needs of cancer patients. This counseling is arranged by the PN and performed by different course leaders of the Cancer Society of the Saarland. Different offers are available: nutrition course, nutrition advice via telephone, art and creative course, music therapy, Nordic walking, QiGong, yoga, and psycho-social or psychological advices.

The forth module of the intervention was also created by the German Cancer Society. It is a ring folder, which is given to all patients at the time of their agreement. With this folder patients can collect and organize all information concerning physician or any other consulting contacts, to keep a personal medication list, to document physical complaints and to collect any discharge letter in a structured way. This folder is not only intended to improve the self-management capabilities of patients, but also to minimize informational deficits in the case of a change of care providers. In this way, patients can find other specialists and hand them over their entire treatment documentation as needed.

For any participating physician a hotline of oncologists was established. The hotline is called “onco-expert-phone” and provides the physicians fast and anytime with unbureaucratic help in case of treatment issues.

### Outcomes

#### Primary outcome

The primary outcome is the health-related quality of life (HRQoL) particularly the mental component score measured by the SF-12 questionnaire [28, 29] six months after baseline. Patients underwent intervention are supposed to improve their psychological QoL to a greater extent than patients without intervention (comparison of means of study groups). SF-12 is the valid and tested short form of the SF-36 questionnaire [30]. It is used in many cases of cancer research (e.g. [31, 32]). HRQoL is based on self-report questionnaires filled out by the patients themselves.

#### Secondary outcomes

Other measurements and supposed effects by the intervention are:
improvement of self-efficacy measured by the General Self-Efficacy Scale, GSE [33],reduction of psychological distress such as depression (measured by the Patient Health Questionnaire-9, PHQ-9 [34, 35]) or anxiety (measured by the General Anxiety Disorder, GAD-7 [36, 37]),improvement of health literacy measured by the HLS-EU-Q47 [38, 39],improvement of patient satisfaction in health care measured by the Qualiskope-A [40],lower health care costs such as ambulatory and stationary costs, medication costs, costs of psychological therapy,reduction of days of inability to work (DIW).

GSE, PHQ-9, GAD-7, HLS-EU-Q47 and Qualiskope-A are well validated [29, 33, 35, 37, 39, 40]. They are part of the patient questionnaire set which will be sent to the patients. Costs and DIW are identified from secondary data analysis from the three participating statutory health insurance companies.

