**Discussion:**

If PIKKO proves to be effective, recommendations can be made to health organizations, which should lead to the concept being rolled out throughout Germany and included into oncological guidelines. We expect PIKKO to be a useful addition to usual cancer care, helping to improve the quality of life of cancer patients and reduce healthcare costs.

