**Fig. 1 Fig1:**
[figure not shown]
The PIKKO concept and the central patient navigator

This concept is intended to become a well-established program in the German health care system for all cancer patients. But before that the PIKKO concept must be evaluated. The evaluation focuses on patients and their health-related quality of life (HRQoL) particularly the mental component. We expect that patients who underwent PIKKO report a higher HRQoL, less mental impairment such as depression and anxiety, better self-management and higher health literacy than patients of the control group. Furthermore, we expect lower direct health care costs (days of inability to work, sick-pay, expenses of health benefits).

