### Data collection methods

According to the four aspects of this evaluation, four different kinds of data are obtained from four different sources.

Up to five times the patients will be asked to fill out a set of questionnaires. The length of these sets varies between 12 and 20 DINA4-pages. With the length and the allocation, the content of the set differs too (see Table 1). Questionnaire sets of the intervention group are longer than of the control group because they included questions about the frequency of use and quality of PIKKO interventions. All questionnaire sets included the six validated questionnaires SF-12 (main outcome, HRQoL, Cronbach’s α = 0.76–0.90 [29]), GSE (self-efficacy, Cronbach’s α = 0.80–0.90 [33]), PHQ-9 (depression, Cronbach’s α = 0.88 [35]), GAD-7 (anxiety, Cronbach’s α = 0.89 [37]), Qualiskope-A (patient satisfaction in health care, Cronbach’s α = 0.87–0.94 [40]) and HLS-EU-Q47 (health literacy, Cronbach’s α = 0.97 [39]). We chose the written form of patient survey because of the expected age structure of the patients. In 2013, the mean age of onset of cancer in Germany was 67.2 (female) and 68.3 (male) years [42]. In 2017, only 61% of people older than 65 used the internet privately [43], but the use of the internet is a prerequisite for online surveys. In a written survey, a much higher response rate is expected.

The second data source is data from the health insurance companies. Different types of values are summarized (see Table 2). These data are pseudonymized and cannot be matched with questionnaire data.

**Table 2 Tab2:** Additional pseudonymized secondary outcomes and time of measurement

Measure	Source	Time of measurement
Economic data		
Demographics	Statutory health insurance companies	6 months after closing recruitment separated in allocation groups
Diagnoses	Statutory health insurance companies	
Ambulatory costs	Statutory health insurance companies	
Stationary costs	Statutory health insurance companies	
Costs of psychological therapy	Statutory health insurance companies	
Medication costs	Statutory health insurance companies	
Days of inability to work	Statutory health insurance companies	
Oncological knowledge database		
Usage data: number of visits, visited subpages, printed content, online time	German Cancer Society	6 months after closing recruitment of the intervention group

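### The cost outcome is defined inconsistently, leaves sick-pay out of the planned extract and lists no cost for PIKKO itself, so as listed it can show a change in insurer cost but not a net reduction in healthcare costs

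*Protocol article*

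**What the plan says.** The protocol article describes the cost outcome in four places.

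- Abstract, Methods: "the time course of direct costs of medical care (e.g. work disability days" are to be analysed. The example is a number of days.
- Methods/design, Objectives (text after Fig. 1): "we expect lower direct health care costs (days of inability to work, sick-pay, expenses of health benefits").
- Secondary outcomes: "lower health care costs such as ambulatory and stationary costs, medication costs, costs of psychological therapy", with days of inability to work (DIW) as a separate outcome. The source is given as follows: "Costs and DIW are identified from secondary data analysis from the three participating statutory health insurance companies".
- Data collection methods, Table 2: the economic extract consists of demographics, diagnoses, four cost categories (ambulatory, stationary, medication and "Costs of psychological therapy") and DIW.

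Statistical methods then compares group averages for health care costs along with the other outcomes. The Abstract's Discussion expects PIKKO to be useful in "helping to improve the quality of life of cancer patients and reduce healthcare costs", and the end of the Background says the cost results should inform implementation and transfer to other diseases.

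On the programme's own cost, the article says only this, under Sample size calculation: "The financing of the PIKKO supply concept was calculated for a maximum of 1.800 patients per group". It gives no unit cost and names no payer. Under Intervention, the third module, provided by the Cancer Society of the Saarland, offers "nutrition course, nutrition advice via telephone, art and creative course, music therapy, Nordic walking, QiGong, yoga, and psycho-social or psychological advices".

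**The concern.** There are two faults. First, the hypothesis and the extract do not match: sick-pay is expected to fall, but no sick-pay amount is listed for collection. A count of days cannot stand in for it without a further rule for turning days into expenditure, and the article gives none.

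Second, PIKKO adds resources in the intervention group only, chiefly navigators, counselling and courses, and database access, together with a hotline for participating physicians. None of these is an identified item in the cost comparison. A difference in insurer cost is a legitimate quantity, but it is not the difference in healthcare cost that the article expects to find. A reader deciding whether to implement or transfer the programme needs the latter.

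**Working it through.** The plan has no cost figure to reproduce. Its one sample-size figure concerns the SF-12 outcome: d = 0.25, two-sided α = 0.05 and power 0.90 give 337.2 per group, rounded up to 338. It reproduces and is unaffected by this point.

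**Step 1: the definitions side by side.**

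| Item | Abstract, Methods | Objectives | Secondary outcomes | Table 2 |
|---|---|---|---|---|
| DIW | yes, as a direct cost | yes, as a direct cost | yes, as a separate outcome | yes |
| Sick-pay amount | no | yes | no | no |
| Health-benefit expenses | no | yes, undefined | not under that name | not under that name |
| Ambulatory, stationary, medication, psychological therapy | not by name | not by name | yes (open list) | yes |
| PIKKO programme cost | no | no | no | no |

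DIW is classed as a direct cost in two places and as a separate outcome in a third. Sick-pay appears once and is not carried into the extract. The list under Secondary outcomes is open, so the omission of sick-pay rests mainly on Table 2, which sets out the data to be supplied.

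**Step 2: what the endpoint can show.** Let x be the insurer cost avoided per intervention patient, and c the programme cost per intervention patient that is not captured in the insurer data. Then:

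- saving shown by the endpoint = x
- net saving = x − c

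The documents give neither x nor c. With assumed values, in any currency unit:

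| x | c | shown | net |
|---|---|---|---|
| 100 | 0 | 100 | 100 − 0 = 100 |
| 100 | 100 | 100 | 100 − 100 = 0 |
| 100 | 300 | 100 | 100 − 300 = −200 |
| 100 | 500 | 100 | 100 − 500 = −400 |
| 300 | 100 | 300 | 300 − 100 = 200 |
| 300 | 500 | 300 | 300 − 500 = −200 |

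The endpoint equals the net only when c = 0, that is, when every PIKKO service is already visible in insurer data. The sign reverses whenever c > x.

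**Step 3: the component that overlaps with a PIKKO service.** Psychological therapy is a listed insurer cost that is expected to fall, and PIKKO itself supplies psychological advice. If that advice replaces billed therapy, the listed cost falls while part of the care has moved to another provider. If it uncovers unmet need, which the Intervention section gives as the purpose of the counselling, billed therapy may rise. The direction is unknown. It cannot be resolved patient by patient, because Data collection methods states that insurer data cannot be matched to the questionnaires, where use of the modules is recorded.

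**The case against.** The strongest reply is that the endpoint is framed as insurer-recorded direct cost, reported by category, and that the article defines no cost-effectiveness or net-cost analysis. Costing perspective and programme cost may be set out in a full protocol or analysis plan that is not shown. That is fair as regards detail. It does not explain why sick-pay is in the hypothesis but not in the extract, since the article states both, and it does not support describing a result in insurer cost as reduced healthcare costs.

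Several stronger readings are tempting, and the documents do not support them.

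- *That care shifts from insurer billing to project-funded services and would be booked as a saving.* The financing statement names no payer. The three insurers helped initiate PIKKO and offer it to their own members, and the article does not say whether its services appear in their data. This can happen; it is not shown that it does.
- *That benefit spending as a whole is left out.* The term in the Objectives may simply mean insurer spending on health services, which the four listed categories could cover. Only sick-pay is clearly missing.
- *That the listed items systematically favour the intervention.* For psychological therapy the direction is open, as shown in the working.
- *That roll-out depends on the cost result.* The Abstract makes recommendations conditional on effectiveness in general, and the primary outcome is the SF-12.
- *That a euro shortfall per patient can be stated.* The article gives no salary and no navigator hours. It says only that up to ten people can be trained, drawn from staff already working in cancer care. The 507 per group is the recruiting aim for the questionnaire evaluation, whereas the programme is financed for up to 1,800 per group, so dividing programme cost by 507 would use the wrong denominator.

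**Conclusion.** The point holds in two parts. The cost outcome is described inconsistently across four places, with sick-pay hypothesised but not listed for extraction. As listed, the costs include no identified cost of PIKKO, so a lower figure in the intervention group supports a statement about insurer cost and not one about net healthcare cost.

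The size cannot be computed from the documents. The sign-reversal condition, c > x, is an identity and needs no assumed prices. Whether it matters in practice depends on one fact the article does not give: how much of PIKKO's cost is already visible in insurer data. If all of it is, this part of the point falls away and the article need only say so.

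This concerns a secondary outcome and leaves the SF-12 comparison untouched. It deserves correction because the article states the expected conclusion on costs and intends the cost results to inform implementation and transfer.

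**What to change.** 1. Use one definition of the cost outcome in the Abstract, Objectives, Secondary outcomes and Table 2. Keep DIW as a count, separate from costs, and say what health-benefit expenses means.
2. Add sick-pay expenditure to the insurer extract, or remove it from the hypothesis.
3. Report the average PIKKO programme cost per intervention patient (navigators, counselling and courses, database, hotline) from project accounts beside the insurer costs. Divide by the patients in the programme, not by the questionnaire sample, and count once any PIKKO service already billed to insurers. A group average is enough, since individual linkage is not available.
4. Base any statement that PIKKO reduces healthcare costs on the net figure. Otherwise limit the conclusion to insurer-billed costs.
5. Report psychological therapy cost as a component without a pre-set beneficial direction.

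The cost is one group-level line from existing accounts, one further insurer field if sick-pay is kept, and some rewording. The downside is a little accounting work and a cost result that may look less favourable.
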